## Abstract

**Background:**

Falls are a common cause of injuries and hospitalization among older adults. While conventional balance training appears effective in preventing falls, a relatively large number of training sessions are needed and retention of the effects after the training period is hard to accomplish. This may be because these interventions are not sufficiently task-specific for the mechanism of falls. Many falls in older adults occur due to unexpected external perturbations during gait, such as trips. Therefore, there is increasing interest in perturbation-based balance training (PBT), which is a more task-specific intervention to improve reactive balance control after unexpected perturbations. The literature suggests that PBT may be more effective and require fewer training sessions to reduce falls incidence in older adults, than conventional balance training. We aim to evaluate the effect of a three-session PBT protocol on balance control, daily life falls and fear of falling. Secondly, we will evaluate the acceptability of the PBT protocol.

**Methods:**

This is a mixed-methods study combining a single-blind (outcome assessor) randomized controlled trial (RCT) using a parallel-group design, and qualitative research evaluating the acceptability of the intervention. The study sample consists of community-dwelling older adults aged 65 years and older who have recently fallen and visited the MUMC+ outpatient clinic. Subjects are randomized into two groups. The control group (*n* = 40) receives usual care, meaning referral to a physical therapist. The intervention group (*n* = 40) receives usual care plus three 30-min sessions of PBT in the Computer Assisted Rehabilitation Environment. Subjects’ balance control (Mini-BESTest) and fear of falling (FES-I) will be assessed at baseline, and 4 weeks and 3 months post-baseline. Daily life falls will be recorded with falls calendars until 6 months after the first follow-up measurement, long-term injurious falls will be recorded at 2-years’ follow-up via the electronic patient record. Acceptability of the PBT protocol will be evaluated with semi-structured interviews in a subsample from the intervention group.

**Discussion:**

This study will contribute to the evidence for the effectiveness of PBT using a training protocol based on the available literature, and also give much needed insights into the acceptability of PBT for older adults.

**Trial registration:**

Nederlands Trial Register NL7680. Registered 17-04-2019 – retrospectively registered.

**Supplementary Information:**

The online version contains supplementary material available at 10.1186/s12877-020-01944-7.

## Background

Falls are a common cause of injuries and hospitalization among older adults [1]. Each year, one in three adults aged 65 years or older, and one in two adults above the age of 80 years, experience a fall [2]. In the Netherlands, around 108,000 older adults (332 per 10.000) visited the emergency department in 2018 after a fall incident, and 33% of them were subsequently admitted to hospital [3]. Falls are putting increasing demands on healthcare resources, with fall-related medical costs in the Netherlands of about 960 million euros in 2018 [3]. If the incidence of falls remains unchanged, and with the aging of the population expected to increase, the number of falls in adults aged 65 years and older will have increased by 47% by 2050 [3]. Falls often have serious physical consequences, such as fractures or head injuries [4]. In addition, there are psychological consequences of falling, which can have a strong negative impact on quality of life [5]. Up to 73% of older adults who have experienced a fall are afraid of falling again, which in turn can lead to decreased physical and social mobility [6]. Once an older adult has experienced a fall incident, their risk of sustaining future falls is greatly increased (OR 2.8 for all fallers, and 3.5 for recurrent fallers) [5, 7].

A modifiable risk factor that has repeatedly been identified in the literature is the presence of gait or balance problems [2, 5, 8]. Many studies have shown that balance training can effectively reduce falls incidence in older adults, with or without specific disorders, by approximately 24% [9–14]. However, the optimal type, duration and frequency of balance training to reduce falls are not yet clear. Berg et al. described three aspects of balance, which should be functionally adequate to accomplish functional balance [15]. The first is the ability to maintain various postures, also referred to as static balance control. The second, is the ability to make postural responses to voluntary changes of body position, using mostly proactive balance control. The third is the ability to react to unexpected external disturbances (perturbations) of balance, also called reactive balance control [15].

Conventional balance training has mostly focused on the first two aspects of balance, where proactive mechanisms of balance control are the most important [16]. While conventional balance training interventions appear effective in preventing falls, a relatively large number of training sessions are needed and retention of the effects after the training period is hard to accomplish [17–19]. This may be because many falls in older adults occur as a result of an unexpected external perturbation during gait, such as a slip or a trip [20, 21]. The unexpected nature of such external perturbations forces individuals to rely mostly on reactive balance control. Since balance training seems highly task-specific, it is not likely that training proactive balance control will also improve reactive balance control, in view of the additional speed and stability requirements of these balance reactions [22].

During the process of physiological aging, changes in the body lead to less efficient reactive balance control strategies, such as delayed onset of muscle responses, decreased magnitude of postural responses, and an increased level of co-activation in muscles [23–25]. Even in community-dwelling older adults who walk independently, there may be a substantial decline in reactive balance control, but this will not become evident until a slip or a trip occurs [26]. Despite this decline, the potential to adapt and improve reactive balance control through training seems to be retained with age [27], leading to an increasing interest in perturbation-based balance training (PBT) [28].

PBT is a form of training that aims to improve reactive balance control after unexpected external perturbations. In a safe and controlled environment, participants are repeatedly exposed to destabilizing perturbations during various activities of daily living. Many different training setups can be utilized, from fairly simple lean-and-release perturbations requiring only a safety harness, to advanced systems that can provide a wide variety of perturbation types and intensities during various tasks.

Studies of PBT have shown significant reductions in falls in older adults with and without specific disorders such as Parkinson’s disease or stroke (with a relative risk of falls of 0.71 [95% CI 0.52–0.96] compared to various control groups) [29–36]. Adaptation may occur faster with this type of training than with conventional balance training, offering the potential of achieving equal or better results with fewer training sessions [34]. For example, a study by Pai et al. showed a 50% reduction in the incidence of daily-life falls during 12 months of follow-up after only a single training session [34].

In an earlier review, we included eight studies on PBT in older adults [28]. We concluded that PBT appears to be a feasible approach to falls prevention in clinical practice, and that a combination of types and directions of perturbation might offer the greatest benefits. Frequency and volume of training varies greatly between studies, and while there are studies showing positive effects with relatively low training doses, the optimal training characteristics are not yet clear. In this study protocol, we describe a PBT protocol including multiple types and directions of perturbations, with a training dose that we hypothesize to be suitable based on the current evidence [28].

Besides improving balance and reducing falls incidence, PBT can significantly reduce the fear of falling [37]. Fear of falling can have a major impact on older adults. While it may initially be a reasonable response to experiencing a fall, and may lead to more cautious behavior, it can also have debilitating consequences when it leads to activity restriction [6]. If this occurs, fear of falling can lead to physical deconditioning and frailty, which can set off a negative spiral by increasing the risk of recurrent falls [38].

While the body of evidence for the effectiveness of PBT for falls prevention is growing, there are other factors to consider [8, 32, 34–36, 39–41]. The perturbations applied in these studies are of such a magnitude that they may not be acceptable to all older adults. Even the most effective interventions are likely to fail if they are not acceptable to the target population. Therefore, the literature recommends combining quantitative and qualitative methods to assess both the effectiveness and acceptability of a new intervention [42]. In this study, we will assess the acceptability of our training protocol through semi-structured interviews, utilizing the definition and theoretical framework of acceptability (TFA) described by Sekhon et al. [43].

This study protocol describes a mixed-methods study combining an outcome-assessor blinded randomized controlled trial (RCT), using two parallel groups (1:1) and a superiority design, with qualitative research concerning the acceptability of the intervention. The primary aim is to determine the effect of our three-session PBT intervention on balance control measured with the Mini-BESTest in community-dwelling older adults (≥65 years) who visit the outpatient clinic after a fall, in comparison to usual care. Secondly, we aim to determine the effect on real-life falls incidence during a 6 months follow-up period. We will also evaluate the effect on fear of falling measured with the Falls Efficacy Scale International (FES-I). A long-term follow-up evaluation will take place at 2 years post-baseline when each subjects’ electronic patient record (EPR) will be checked with the aim of investigating the long-term effect of PBT on injurious falls.

Lastly, we aim to determine the acceptability of our three-session PBT protocol through semi-structured qualitative interviews in a sub-group of the intervention group in this study.

## Methods

### Study design

This is a mixed-methods study combining a single-blind (outcome assessor) randomized controlled trial (RCT) in a parallel-group design, with qualitative research to assess the acceptability of the intervention. This protocol was written in accordance with the Standard Protocol Items: Recommendations for Interventional Trials (SPIRIT) checklist. The study will be conducted at MUMC+ in Maastricht, the Netherlands from March 2019 until July 2021. The study was approved by the Medical Ethics Committee azM/UM (METC18–049).

### Subjects

Community-dwelling older adults (65+) who have experienced a fall in the past 3 months and visit the MUMC+ outpatient clinic will be approached to participate in this study. To ensure that our sample includes only older adults at increased risk for falling, persons who fell during exercise activities (i.e. cycling) or due to actions of a third party, will be excluded. Similarly, persons using medication that is known to increase the fall risk will be excluded from this study. For a full description of the eligibility criteria, see Table 1.

**Table 1 Tab1:** Full eligibility criteria

Inclusion criteria	Exclusion criteria
Age ≥ 65 years	Diagnosed with osteoporosis
Community-dwelling	Recent fracture or severe contusion of the lower extremities, back or shoulders (in consultation with medical doctor)
Able to walk without a walking aid for ≥15 min	Any disease or disorder that may influence the safety of training (e.g. severe cardiopulmonary disease)
Recently having experienced a fall (≤3 months ago)	Falls caused by actions of third parties or during exercise activities
Having visited the MUMC+ outpatient clinic after their fall incident	Uncorrected vision problems
	Falls due to syncope
	Use of medication known to increase fall risk (antidepressants, benzodiazepines, sedatives, hypnotics, antipsychotics) [44]
	Use of painkillers that can decrease responsiveness (e.g. morphine, oxycodone) [44]
	Inability to provide written informed consent and communicate in Dutch
	Inability to follow instructions due to cognitive problems

### Recruitment, randomization, blinding and treatment allocation

Eligible patients will be informed about this study by their medical doctor when they visit the outpatient clinic of the MUMC+. If patients are interested in the study, they will receive written information and will be asked for their permission to be phoned by the investigators. Patients are given the opportunity to read the study information at home and will be phoned by the investigators 3 to 7 days later. If a patient wants to participate, an appointment will be scheduled to visit the MUMC+ department of physical therapy. During this visit, any remaining questions will be answered and written informed consent will be obtained.

After this, the investigator will check the eligibility criteria. If the subject meets the criteria, baseline measurements will be performed. When these have been completed, the subjects will be randomized to the intervention- or control group. This will be done using a 1:1 ratio stratified block randomization (block sizes 2 and 4 will be randomized). Randomization will be stratified based on sex (male versus female) and number of falls during the past year (1 versus 2 or more). This stratification will result in four different strata. The randomization sequence will be generated using an online random number generator. The allocation will be concealed by using sequentially numbered, sealed opaque envelopes. The person preparing the allocation concealment mechanism will be a different person than the one enrolling the subjects and assigning them to a group. The allocation sequence list will be kept in a locked drawer, which can be accessed only by the principal investigator.

### Timeline

The first study visit for subjects consists of two parts; t_− 1_ is where subjects make their final decision on participating in the study, informed consent is obtained and the eligibility criteria are checked. If a subject meets all eligibility criteria, this visit is combined with t_0_. At t_0_, baseline measurements are performed by the outcome assessor, which will be blinded to treatment allocation. Subjects are explicitly instructed to hide their treatment allocation from this researcher. If the treatment allocation of an individual subject is revealed to the outcome assessor, a second blinded outcome assessor will take over the remaining measurements. After baseline measurements, the subject is randomized to the control- or intervention group by the same researcher that enrolled the subject in the study. For subjects in the intervention group, this visit is followed by three training sessions in 3 weeks. Both groups have their t_1_ visit at 4 weeks post-baseline, and a t_2_ visit 3 months after that, t_2_ being the last study visit for subjects. From t_0_ on, all subjects will fill in falls calendars until 6 months after t_1_. A final check of the EPR at t_3_, 2 years post baseline, concludes data collection for this study. An overview of the study timeline is presented in Table 2.

**Table 2 Tab2:**
[figure not shown]
Patient flow of enrolment, assessments and interventions

### Interventions

Subjects in this study will be randomized to the control group (usual care) or the intervention group (usual care + PBT). Training in the intervention group will be provided by specifically trained physical therapists in association with clinical operators of the CAREN system.

### Control intervention (usual care)

All included subjects will receive usual care. Usual care in the MUMC+ outpatient clinic consists of a referral for physical therapy treatment for the injuries sustained during the fall incident, if the medical doctor determines that this is indicated (for example, mobility and strength exercises after a shoulder fracture). During the study, the outcome assessor will monitor whether each subject has used their referral to visit a physical therapist, how many times, and what components (i.e. strength training, mobility exercises, balance exercises) were included in the physical therapy treatment.

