### Outcomes

#### Balance control (main outcome)

The main outcome in this study is balance control, which will be measured with the Mini Balance Evaluation Systems Test (Mini-BESTest). The Mini-BESTest has been identified as the most comprehensive measurement tool to assess balance in community-dwelling older adults [46]. It measures balance in four categories: proactive balance, reactive balance, sensory orientation and dynamic gait. Each of the 14 tasks is scored on a three-point scale, with a total score that can range from 0 to 28 points. A higher score corresponds with better balance control. Proactive balance is tested using a sit-to-stand transfer where the subject has to try not to use their hands, standing on tiptoes, and standing on one leg. Reactive balance is tested with therapist-applied lean-and-release perturbations in the forward, backward and sideways directions. Sensory orientation is tested by standing with feet together, standing with feet together and eyes closed on a foam surface, and standing on a slope with eyes closed. Dynamic gait is tested with five tasks; suddenly changing gait speed, walking while turning the head left and right, walking and turning, stepping over an obstacle while walking, and Timed Up and Go performance. The Mini-BESTest has good psychometric properties [47, 48]. Cut-off values indicating increased fall risk for the Mini-BESTest are age dependent; ≤25 points for people 60 to 69 year of age, ≤23 points for 70 to 79 years, ≤22 points for 80 to 89 years and ≤ 17 points for 90 years and older [49]. The minimal detectable change on the Mini-BESTest is 3.5 points and the minimal important change is 4 points [47]. Balance control will be measured at baseline, T_1_ and T_2_.

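### The blinded outcome assessor is also given the task of monitoring each subject's physical therapy visits and content, which creates an avoidable risk of accidental disclosure of the allocation

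*Protocol article*

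**What the plan says.** The Study design section describes "a mixed-methods study combining a single-blind (outcome assessor) randomized controlled trial (RCT) in a parallel-group design". The Timeline section says that "baseline measurements are performed by the outcome assessor, which will be blinded to treatment allocation" and adds: "Subjects are explicitly instructed to hide their treatment allocation from this researcher". If an allocation does become known, a second blinded assessor does what is left to measure for that subject.

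The section on usual care gives the same role a further task: "the outcome assessor will monitor whether each subject has used their referral to visit a physical therapist, how many times, and what components" the treatment had. Work on strength, on mobility and on balance are the three kinds of component that the section lists.

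On the experimental side, the Interventions section says: "Training in the intervention group will be provided by specifically trained physical therapists in association with clinical operators of the CAREN system". The Training setup section places this training in the hospital's physical therapy department.

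For the main outcome, the article says "Balance control will be measured at baseline, T_1_ and T_2". The FES-I is collected at the same time points, with the outcome assessor helping the subject to fill it in.

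**The concern.** The person who must not learn the allocation is asked to inquire into the area of care where the two arms differ. In both arms the subject may have seen a physical therapist, and in both arms that treatment may have included balance work. In the intervention arm there were also up to three sessions of balance training with physical therapists. A subject asked about therapist visits and balance exercises can easily mention those sessions without meaning to.

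What is at stake is detection bias. Subjects, treating therapists and the researcher who randomises all know the allocation, so the assessor's blinding is the protection in force while outcomes are being collected. The Mini-BESTest is scored by a rater on three-point items, and its reactive items depend on a push or release applied by the tester. Knowledge of the allocation could therefore affect both the stimulus and the score, on the kind of balance that PBT is meant to train. The FES-I is exposed to a lesser degree, through the assessor's help with completion.

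**Working it through.** No figure in the plan bears on this point, so the check sets the sections side by side.

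1. **Who collects physical therapy use?** The outcome assessor, for each subject, during the study (Control intervention). This is stated, not left open.
2. **What is collected?** Whether the referral was used, the number of visits and the components, with balance exercises named (same section). The referral is for injuries from the fall, if the doctor finds it indicated, and belongs to usual care in both arms.
3. **Is that role blinded?** Yes (Study design; Timeline). The Statistical analysis section also blinds the data analyst, so the assessor is the only role blinded during data collection, not the only one in the trial.
4. **Does the topic overlap with the experimental treatment?** Yes in kind, provider and place: balance training (Experimental intervention), by physical therapists (Interventions), in the physical therapy department (Training setup). It does not overlap in route, because PBT is a study intervention and is not given through the referral.
5. **What does the role measure?** The Timeline has it perform the baseline measurements, and its replacement rule implies the later ones too. These include the Mini-BESTest, whose T1 value is the primary endpoint.
6. **What protects against a slip?** The instruction to conceal, and the replacement assessor. The second acts only once a disclosure has been recognised, and only on later measurements. A partial hint that is not recognised as one goes uncorrected.
7. **Does any section give the task to someone else, or place it after scoring?** None does. The assessment schedule (Table 2) is not shown, so the order within a visit is unknown.

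For size, let p be the share of intervention subjects whose allocation reaches the assessor by this route before scoring, q the share of those recognised and handed over in time, and d the mean shift in score among the rest. If scoring in the control arm is unaffected, the shift in the between-group difference is p × (1 − q) × d. The article gives none of the three, so no value follows from it.

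**The case against.** The strongest reply is that the question is narrower than it looks. It asks about the usual-care referral for fall injuries, and a subject in either arm can report the number of visits and the exercises done without touching on PBT. That stands. A reader might infer that intervention subjects must either reveal PBT or give an incomplete answer, and hence that co-intervention data will be less complete in one arm. The text does not support either inference. What remains is the chance of a slip when older adults have to keep two kinds of physical therapy apart in conversation.

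Second, the article anticipates disclosure and provides for it. This also stands in part: an open mention of the treadmill system or the harness would be noticed, and the replacement rule would apply. The rule does not reach hints that pass unnoticed or scores already given.

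Third, the article says that the assessor monitors this, not that the assessor asks, and gives no mode, timing or order relative to scoring. Asking the subject is an inference, though a natural one, since no other source for visit counts and content is named. Order within a visit is a detail that a condensed article may leave to the full protocol, so its absence is not the point here. The point is the assignment of the task, which the article does state.

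**Conclusion.** The point holds as an avoidable exposure of the assessor's blinding, with partial safeguards already in place. It rests on two assumptions: that monitoring involves contact with the subject or the therapy record, and that the assessor who monitors is the one who scores the later visits. Both are the natural reading of the text.

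The size of any bias cannot be estimated from the document. A reader might go further and infer that the primary result will be biased, that the sections contradict each other, or that the trial has no other blinding. None of these is supported. The monitored item can be answered without disclosure, the two tasks can coexist, and the analyst is blinded as well, although analyst blinding cannot correct a score that was biased when given. If the item is in fact collected only after scoring, the T1 comparison is protected from anything said at that visit. The change is still worth making, because it removes a threat to the main outcome by reassigning an existing task.

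**What to change.** In Control intervention (usual care), replace the outcome assessor with the researcher who enrols and randomises, who already knows the allocation. Collect physical therapy use on a standard form sent with the monthly falls calendar, or by phone, with the same wording and timing in both arms. Have the forms returned to that researcher and kept from the assessor until the subject's T2 measurements are complete.

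If the assessor must keep the task, state that it is done only after the Mini-BESTest and FES-I have been scored at each visit, and not between visits. This is weaker: it protects T1, but a disclosure at T1 still carries over to T2 unless the replacement rule is triggered. In either case, record each disclosure and the visit at which it occurred.

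The cost is small. Monthly postal returns and phone contacts are already planned under Prospective falls incidence, so no new visit or staff role is needed. The downside is that the person recording this process variable knows the allocation and might probe differently by arm. A self-completed standard form limits this.
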